**E. Third Elevated BP in last 24 months at healthcare maintenance or non-acute care visit**

If this is the initial visit which qualifies a patient for BP-CATCH, this must be a healthcare maintenance or non-acute care visit. If this patient previously had a qualifying BP-CATCH elevated BP visit above, then this can be any visit when the patient returned for BP follow-up.

1. Date of visit with third or more elevated BP noted (MM/DD/YYYY): \_\_/\_\_/\_\_\_\_ [THESE DATA ARE ENTERED INTO REDCAP BUT NOT GIVEN TO RESEARCH TEAM]

1a. Height at this visit with an elevated blood pressure \_\_\_\_\_ (centimeters) ☐ Not done at this visit

1b. Weight at this visit with an elevated blood pressure \_\_\_\_\_ (kilograms) ☐ Not done at this visit

2. Systolic Blood Pressure: \_\_\_\_\_ Systolic Percentile: \_\_\_\_\_ ☐ Percentile unknown

3. Diastolic Blood Pressure: \_\_\_\_\_ Diastolic Percentile: \_\_\_\_\_ ☐ Percentile unknown

4. Blood pressure measured by: ☐ Automated (Oscillometry) [Go to 4a] ☐ Manual (Auscultation) [Go to 4c]

4a. Was this BP repeated by manual (auscultation)? ☐ Yes [Go to 4b] ☐ No [Go to 4a.i.]

4a.i. Was automated BP still elevated ( $\geq$  90th percentile for patient's height, weight and sex, or  $\geq 120/80$ )?

☐ No [STOP COMPLETING FORM]

☐ Yes ( $\geq$  90th percentile for patient's height, weight and sex, or  $\geq 120/80$ ) [Go to 5]

4b. What were manual BP results:

Systolic Blood Pressure: \_\_\_\_\_

Diastolic Blood Pressure: \_\_\_\_\_

4c. Was BP re-measured again with manual ?

☐ Yes [Go to 4c.i] ☐ No [Go to 4e]

4c.i. If Yes, what were additional results: Systolic Blood Pressure #2: \_\_\_\_\_

Diastolic Blood Pressure #2: \_\_\_\_\_ [Go to 4d]

4d. Was average of 2 manual BPs still elevated ( $\geq$  90th percentile for patient's height, weight and sex, or  $\geq 120/80$ )?

☐ Yes [Go to 5] ☐ No [STOP COMPLETING FORM]

4e. Was first manual BP elevated ( $\geq$  90th percentile for patient's height, weight and sex, or  $\geq 120/80$ )?

☐ Yes [Go to 5] ☐ No [STOP COMPLETING FORM]

5. Did provider document that the following were discussed with patient and/or family:

5a. Weight counseling ☐ Yes ☐ No ☐ N/a patient has normal BMI

5b. Nutrition counseling ☐ Yes ☐ No

5c. Lifestyle modifications ☐ Yes ☐ No

6. Did the patient have BP in Stage II Hypertension range ( $\geq 95$ th+12mm to <95th+30mm; or  $\geq 140/90$  to <180/120)?

☐ Yes [Go to 6a] ☐ No [Go to 7]

6a. Did the patient have BP in Stage II Hypertension range ( $\geq 95$ th+12mm to <95th+30mm; or  $\geq 140/90$  to <180/120) at the prior visit?

☐ Yes [Go to 6b] ☐ No [Go to 7]

6b. Did the provider document a diagnosis of 'Stage II Hypertension' in notes, billing or problem lists at this visit?

☐ Yes [Go to Section F] ☐ No [Go to Section F]

7. Did the patient have BP in Stage I Hypertension range ( $\geq 95^{\text{th}}$  to  $< 95^{\text{th}} + 12\text{mm}$  or 130/80 to 139/89)?

☐ Yes [Go to 7a] ☐ No [Go to 8]

7a. Did the provider document a diagnosis of 'Stage I Hypertension' in notes, billing or problem lists at this visit?

☐ Yes [Go to Section F] ☐ No [Go to Section F]

8. Did the provider document a diagnosis of 'Elevated Blood Pressure (or BP)' in notes, billing or problem lists at this visit?

☐ Yes [Go to Section F] ☐ No [Go to Section F]

## F. Actions Taken

1. What co-morbidities does the patient have or is suspected of having based on documentation in the chart?

☐ Diabetes ☐ Abnormal renal function (e.g. elevated Cr) ☐ Obesity/Overweight ☐ Obstructive Sleep Apnea

☐ Growth Delay ☐ Endocrine disease history ☐ Social concerns (e.g. drug use, school truancy, etc.)

☐ Other: \_\_\_\_\_

2. Were any relevant BP laboratory evaluations completed on this patient? ☐ Yes [Go to 3] ☐ No [Go to 5]

3. Date of first laboratory evaluations *resulted* (MM/DD/YYYY): \_\_/\_\_/\_\_\_\_ [THESE DATA ARE ENTERED INTO REDCAP BUT NOT GIVEN TO RESEARCH TEAM]

\*Not date laboratory evaluation ordered or sent, but date labs actually *resulted* back to clinic

4. Which laboratory evaluations have *resulted* since patient had 2nd or 3rd elevated BP readings (Check all that apply)?

☐ CBC ☐ Chemistry Panel (Cr, BUN, electrolytes) ☐ Urine Analysis ☐ Fasting Serum Glucose

☐ Lipids ☐ AST/ALT ☐ HgA1c ☐ TSH ☐ Drug screen

☐ Other: \_\_\_\_\_

5. Were any relevant radiologic or other evaluations *completed* on this patient? ☐ Yes [Go to 6] ☐ No [Go to 8]

6. Date of first radiologic or other evaluations *resulted* (MM/DD/YYYY): \_\_/\_\_/\_\_\_\_ [THESE DATA ARE ENTERED INTO REDCAP BUT NOT GIVEN TO RESEARCH TEAM]

\*Not date radiologic or other evaluations ordered or completed, but date actually *resulted* back to clinic

7. Which radiologic or other evaluations have resulted (Check all that apply)?

☐ Renal US ☐ Sleep Study ☐ CTA ☐ MRA

☐ Other: \_\_\_\_\_

8. If laboratory evaluations or radiologic/other evaluations were abnormal, was a referral request to a subspecialist made?

☐ Yes, abnormal results led to a subspecialist referral request [Go to 8a]

☐ No, abnormal results did not lead to a subspecialist referral request [Go to 9]

☐ No referral because all laboratory evaluations and radiologic/other evaluations normal [Go to 9]

☐ Referral request made to specialist but all laboratory evaluations and radiologic/other evaluations normal [Go to 8a]

8a. If yes, what date was referral request *made*? (MM/DD/YYYY): \_\_/\_\_/\_\_\_\_ [THESE DATA ARE ENTERED INTO REDCAP BUT NOT GIVEN TO RESEARCH TEAM]

\*Not date of subspecialist visit, what date did someone in the clinic tell the patient/family they needed to see a subspecialist and complete referral paperwork?

8b. If a subspecialist referral was made, which specialist? (Check all that apply):

☐ Nephrologist ☐ Cardiologist ☐ Other: \_\_\_\_\_

8c. ☐ N/A: Patient never attended subspecialist visit [Go to 9]

[IF N/A NOT CHECKED] Date first subspecialist visit completed (MM/DD/YYYY): \_\_/\_\_/\_\_\_\_ [THESE DATA ARE ENTERED INTO REDCAP BUT NOT GIVEN TO RESEARCH TEAM]

\*Not date referral request made, but date patient actually saw subspecialist

☐

8d. Date information on the patient was received from subspecialist back to the pediatrician:

(MM/DD/YYYY): \_\_/\_\_/\_\_\_\_ [THESE DATA ARE ENTERED INTO REDCAP BUT NOT GIVEN TO RESEARCH TEAM]

\*If same electronic health record, enter date note was signed by the subspecialist

9. Was an ambulatory blood pressure monitoring (ABPM) device used in this patient? ☐ Yes [Go to 9a] ☐ No [Go to 10]

9a. If Yes, who prescribed the ABPM? ☐ Pediatrician ☐ Subspecialist ☐ Other: \_\_\_\_\_

9b. How useful was the information from the ABPM?

☐ Very Useful ☐ Useful ☐ Neutral ☐ Not Useful at All ☐ Do Not Know

10. Were BP readings obtained in the school setting used in this patient? ☐ Yes [Go to 10a] ☐ No [Go to Section G]

10a. If Yes, who prescribed the school setting BPs? ☐ Pediatrician ☐ Subspecialist ☐ Other: \_\_\_\_\_

10b. How useful were the school setting BPs?

☐ Very Useful ☐ Useful ☐ Neutral ☐ Not Useful at All ☐ Do Not Know

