| Secondary Outcome Measures | 
 
1. Number of patients without correct diagnostic and management decisions at specified points per 100 patients with measured elevated BP 
 
a. Re-measuring BP twice in clinic via auscultation
 
b. Weight and nutrition counseling
 
c. Repeat BP measurement visits appropriately timed
 
d. Initial laboratory workup
 
e. Subspecialist referral
 
f. Definitive medication management initiation
 
 
 
2. Mean time from first elevated BP to specific points in diagnostic and management process (see #1 above)
 
3. Number of BPs measured correctly with appropriately screened patient, patient position, cuff size, inflation, BP percentiles correctly documented and interpreted per 100 observations conducted
 
4. Time to 3rd next available subspecialist appointment
 
 |

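### Chart tool item F8 has no true answer for a child with no work-up, which can bias referral outcome 1e and time to referral, depending on how F8 is scored

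*Protocol*

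**What the plan says.** All item numbers refer to the BP-CATCH Chart Review Tool in the protocol appendix.

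- F2 reads "Were any relevant BP laboratory evaluations completed on this patient? ☐ Yes [Go to 3] ☐ No [Go to 5". A No goes on to F5.
- F5 asks the same about radiologic or other evaluations "on this patient? ☐ Yes [Go to 6] ☐ No [Go to 8". A No goes on to F8.
- F8 asks "If laboratory evaluations or radiologic/other evaluations were abnormal, was a referral request to a subspecialist made" and offers four answers. Option 1 is "Yes, abnormal results led to a subspecialist referral request [Go to 8a". Option 2 is "No, abnormal results did not lead to a subspecialist referral request [Go to 9". Option 3 is "No referral because all laboratory evaluations and radiologic/other evaluations normal [Go to 9". Option 4 is a referral request made although all evaluations were normal; like option 1, it leads to 8a, where the referral date is entered.
- Table 2 (Section 4, Pediatric HTN Outcome Measures) lists "Subspecialist referral" as marker 1e and the initial laboratory work-up as marker 1d, both per 100 patients with measured elevated BP. Outcome 2 is the mean time to each marker.

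**The concern.** A child with neither kind of evaluation is routed to a question about what the evaluations showed. No answer says that nothing was done, and there is no N/A box. The person completing the form must record a result that does not exist or leave the item empty.

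Two outcomes draw on this item. Marker 1e needs to know whether a referral was made and whether it should have been. Time to referral needs the date at 8a, which is reached only through options 1 and 4. A child referred without any work-up therefore has no true route to 8a. If option 2 or 3 is ticked, or F8 is left blank, both the referral and its date are lost.

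The affected group should also change in size with the intervention. The laboratory work-up is itself a target (marker 1d), and Section 3 names the pre-referral work-up as a focus of the phase with subspecialists. A recording fault in a group that shrinks under intervention need not cancel between conditions.

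**Working it through.** The protocol gives no figure on this point, so there is none to reproduce. The check is an enumeration of the form followed by an illustration.

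**Step 1: the form.** Cross laboratory done or not, radiologic/other done or not, result, and referral made or not, against the four F8 answers.

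| Evaluations done | Result | Referral | True F8 answers |
|---|---|---|---|
| At least one | Abnormal | Made | 1 |
| At least one | Abnormal | Not made | 2 |
| At least one | Normal | Not made | 3 |
| At least one | Normal | Made | 4 |
| None | None | Made | none |
| None | None | Not made | none |

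**Step 2: can another part of the tool supply the answer?**

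- The guidance equates No with not documented. That does not choose between options 2 and 3, which are both No answers but assert opposite results.
- Referral is also asked at C6c and D7b, but only after abnormal extremity pressures, and at G2a, but only after a completed echocardiogram. None of these covers untested children in general.
- The tool handles the parallel case correctly in Section G: G1 = No skips the echocardiogram referral question.

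**Step 3: which records are affected?** Section F is entered from D6b (Stage II range at this and the prior visit) or from the end of Section E (third or later elevated BP). Other records never reach F8.

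**Step 4: illustration.** Suppose option 2 is scored as a referral error and option 3 as correct. Per 100 Section F records, let u be the untested share (none of them referred), f the share of these ticked as option 2 (the rest option 3), and r the option 2 rate among tested children, equal in both conditions. Then

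apparent errors = 100 × [u × f + (1 − u) × r].

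With a truthful extra answer not counted as a referral error, errors = 100 × (1 − u) × r. The part caused by the tick is therefore 100 × u × f in each condition. If f is equal across conditions, its contribution to the difference is 100 × (u₁ − u₀) × f. All values below are assumptions with r = 20%; the pair 73% and 36.5% borrows the protocol's composite error rate and its hypothesised halving only as a proxy.

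| u, usual care → QIC | f | Usual care | QIC | Difference | Part due to the tick |
|---|---|---|---|---|---|
| 50% → 30% | 0 | 10.0 | 14.0 | +4.0 | 0 |
| 50% → 30% | 0.5 | 35.0 | 29.0 | −6.0 | −10.0 |
| 50% → 30% | 1 | 60.0 | 44.0 | −16.0 | −20.0 |
| 73% → 36.5% | 0 | 5.4 | 12.7 | +7.3 | 0 |
| 73% → 36.5% | 1 | 78.4 | 49.2 | −29.2 | −36.5 |

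The positive differences at f = 0 are not a fault of the form. They arise because more children have results to act on, and a truthful extra answer would give the same figures.

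If ticking habits differ between conditions, the sign is open. With u = 50% in both and f = 20% versus 80%, the difference is 100 × 0.5 × (0.8 − 0.2) = +30 points, or −30 with the habits reversed, where the true difference is 0.

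**Step 5: other scoring.** If options 1 and 4 count as referral made and options 2 and 3 as not made, f drops out. The choice between the two untrue boxes then has no effect on the yes/no split.

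**The case against.** The strongest reply is that the damage depends on a scoring rule the protocol does not state. Marker 1e is named only as subspecialist referral, and the example in Section 4 asks whether a referral was received. Both fit made versus not made, under which the choice of untrue box is harmless. The mapping from F8 to 1e may stand in an analysis plan that is not shown. This is right, and it makes the consequence conditional.

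Other parts of the reply also stand:

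- Marker 1e has all patients with measured elevated BP as its denominator. Section 1.2 reports that over 75% did not return on time for a second or third measurement. The effect per 100 such patients is the effect per 100 Section F records times the share reaching Section F, so it is smaller than the table shows.
- A reader might infer that the untested route is common. The documents give no share, and the Data and Safety Monitoring Plan has sites search for at least two worked-up patients each month, which may reduce it.
- Orientation, shared clarifications and second chart reviews may make ticking more uniform.
- Where laboratory testing was required, the untested child already fails the all-steps primary outcome.

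What does not stand is that an analysis rule alone closes the gap. It can sort the answers that were given. It cannot recover a referral or a date that the form gave no true route to record.

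**Conclusion.** The gap is certain from the skip logic: an untested child who reaches F8 has no true answer. The exposure is mainly secondary outcome 1e and time to referral, and only in Section F records.

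Bias between conditions is possible, not shown. It needs option 2 scored as an error and option 3 as correct, some untested children ticked as option 2, and either an untested share or a ticking habit that differs by condition. Its size is unknown. The illustration gives 0 to 20 points per 100 Section F records for untested shares of 50% and 30% with equal habits, and up to 36.5 with the proxy shares. It treats an untested, unreferred child as no referral error. Where the protocol's definition makes referral due, option 3 would instead hide an error, which is not sized here.

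A reader might infer that the referral comparison cannot be interpreted at all, or that the form by itself pushes the marker both ways. The documents do not support either. Made-versus-not-made scoring largely survives, affected records can be found from F2 and F5, and with equal ticking habits under the illustrated scoring the form's own contribution runs only in the direction in which the untested share moves.

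The point still deserves correction. Section 3 plans to analyse and publish the November 2018 to March 2020 data, and Section 4 continues these outcomes for patients contacted for home monitoring.

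**What to change.** **Form.** Add to F8 the answer *No laboratory or radiologic/other evaluations completed*, split into referral request made (go to 8a) and not made (go to 9).

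**Records already entered.**

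1. Flag every record with F2 = No and F5 = No.
2. From F8, take only referral made (options 1 and 4) or not made (options 2 and 3). Do not use the result wording to score 1e.
3. Treat a blank F8 as missing.
4. Count the absent work-up under 1d.
5. Judge whether referral was due by the protocol's own outcome definition. No new clinical rule is needed.
6. Report the number of flagged records by condition, so that the reach of the problem is visible.

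**Cost.** One response option and one coding rule. F2 and F5 are items of the same form, so flagging needs no new data. It would be too strong to say that no chart needs reopening: blank F8 items, and referrals whose date was never reached, may need a re-check at the site.

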## G. Pharmacologic Management

1. Was an echocardiogram completed on this patient? ☐ Yes [Go to 2] ☐ No [Go to 3]

2. Date of echocardiogram *resulted* (MM/DD/YYYY): \_\_/\_\_/\_\_\_\_ [THESE DATA ARE ENTERED INTO REDCAP BUT NOT GIVEN TO RESEARCH TEAM]

\*Not date echocardiogram ordered or completed, but date actually resulted back to clinic

2a. If echocardiogram was abnormal, was a referral to a subspecialist made?

☐ Yes, abnormal results led to a subspecialist referral [Go to 2b]

☐ No, abnormal results did not lead to a subspecialist referral [Go to 3]

☐ No referral because echocardiogram normal [Go to 3]

☐ Referral made to specialist but echocardiogram normal [Go to 2b]

☐ Patient already referred to subspecialist for echocardiogram [Go to 3]

2b. If yes, what date was referral request *made*? (MM/DD/YYYY): \_\_/\_\_/\_\_\_\_ [THESE DATA ARE ENTERED INTO REDCAP BUT NOT GIVEN TO RESEARCH TEAM]

\*Not date of subspecialist visit, what date did someone in the clinic tell the patient/family they needed to see a subspecialist and complete referral paperwork?

2c. If a subspecialist referral was made, which specialist? (Check all that apply):

☐ Nephrologist ☐ Cardiologist ☐ Other: \_\_\_\_\_

2d. ☐ N/A: Patient never attended subspecialist visit [Go to 3]

[IF N/A NOT CHECKED] Date first subspecialist visit completed (MM/DD/YYYY): \_\_/\_\_/\_\_\_\_ [THESE DATA ARE ENTERED INTO REDCAP BUT NOT GIVEN TO RESEARCH TEAM]

\*Not date referral request made, but date patient actually saw subspecialist

2e. Date information on the patient was received from subspecialist back to the pediatrician:

(MM/DD/YYYY): \_\_/\_\_/\_\_\_\_ [THESE DATA ARE ENTERED INTO REDCAP BUT NOT GIVEN TO RESEARCH TEAM]

\*If same electronic health record, enter date note was signed by the subspecialist

3. Was a medication to treat the patient's hypertension or elevated blood pressure started?

☐ Yes [Go to 4] ☐ No [**STOP COMPLETING FORM**]

4. Who started the medication?

☐ Pediatrician ☐ Nephrologist ☐ Cardiologist ☐ Other: \_\_\_\_\_

5. Date medication ordered (MM/DD/YYYY): \_\_/\_\_/\_\_\_\_ [THESE DATA ARE ENTERED INTO REDCAP BUT NOT GIVEN TO RESEARCH TEAM]

\*Date medication ordered

**Thank you for completing this data entry form**

## Recruitment Email for Specific Providers:

Dear [name],

We reaching out to you as a leader of a pediatric primary care practice. As you know, between 3% and 5% of children have hypertension, and almost 40% of children diagnosed with hypertension already have lifelong heart muscle damage when they are diagnosed. Prior studies suggest pediatricians may be missing elevated blood pressure in their patients more than 80% of the time. For this reason, we are attempting to ensure accurate and timely pediatric hypertension diagnosis and management for all pediatric patients, based on the 2017 AAP guidelines. As part of this research study, we are also looking to better integrate subspecialist and primary care practitioners in this effort, and even move more primary care practitioners towards managing hypertension themselves with subspecialist back-up as needed. We are pursuing this effort led by a group of 10 nationally known pediatric quality improvement, primary care and nephrology researchers. Also, clinics from Johns Hopkins, University of Michigan, Cleveland Clinic, Montefiore Medical Group, and Medical University of South Carolina are already enrolled.

The study will randomize primary care clinics and their associated pediatric subspecialists (nephrologist and/or cardiologist) to one of 3 groups. All groups will get the same quality improvement collaborative intervention in a stepped wedge fashion. The first group will begin working on improving measurement of blood pressure, recognition of elevated blood pressure, and initial steps towards hypertension diagnosis and management. After 6 months, they will incorporate their subspecialist into the collaborative, to improve communication between the primary and subspecialty care realms. Following those 6 months, we will encourage primary care practices to move further with a “hub and spoke” model; their subspecialist will serve as a “hub” for hypertension diagnosis and management questions, to multiple primary care clinic “spokes” who will be doing more and more hypertension care themselves. We anticipate this will benefit subspecialists as they can see more new patients, benefit patients who will not need to travel to a tertiary care center and get more rapid care, and finally primary care physicians who can bill for higher acuity visits and have greater patient continuity. Group 1 will spend the final 6 months of the project sustaining these improvements and changes. Group 2 will proceed similarly through this list with a 6 month “usual care” with data collection phase in the beginning and no sustain phase at the end. Group 3 will have a 12 month usual care phase and not have the intermediate phase where primary and subspecialty care practitioners work on communication and transition issues. Practices will be involved for a total of approximately 29 months as some initial pre-work is needed. We anticipate the collaborative will begin pre-work in winter 2018-2019.

Each practice will be asked to identify and track the care delivered for approximately 10 patients with elevated blood pressure readings (not ‘Elevated Blood Pressure’ diagnosis) each month. They will also join every 6 month video conference day-long learning sessions when they are intervening, and every month 1-hour long collaborative video conferences. Everyone involved can get Part 4 MOC credit, one on one QI coaching, and we hope (but cannot promise until enrollment is complete) to be able to provide some small amount of money to each site to reduce data collection burden.

**If this project still sounds interesting to you, we would first and foremost ask that you identify a primary care practitioner(s) and a pediatric nephrologist or cardiologist who will be your co-leads for this study.** As much of this project is centered around the care delivered in primary care, the primary care co-leader will be essential to its success. We also **suggest that each subspecialist identify at least 2 (or more) clinics** who they can work with, as we want to make sure the subspecialist has enough hypertensive patient volume referred from the primary care clinics to make it worthwhile for them to participate.

**Once you have your partner(s) and if you are still interested, please reach out to me.** We can find days and times when the project leadership and your team can get on a conference call to discuss further specifics and answer any and all questions.

Thank you again for your interest and all the best,  
--[name]

## Recruitment Email for Pediatric Quality Improvement Listserves:

Dear XXX Members,

We are reaching out to you as leaders of pediatric primary care practices. As you know, between 3% and 5% of children have hypertension, and almost 40% of children diagnosed with hypertension already have lifelong heart muscle damage when they are diagnosed. Prior studies suggest pediatricians may be missing elevated blood pressure in their patients more than 80% of the time. **For this reason, we are attempting to ensure accurate and timely pediatric hypertension diagnosis and management for all pediatric patients, based on the 2017 AAP guidelines.** As part of this quality improvement and research study, we are also looking to better integrate subspecialist and primary care practitioners in this effort, and even move more primary care practitioners towards managing hypertension themselves with subspecialist back-up as needed. We are pursuing this effort led by a group of 10 nationally known pediatric quality improvement, primary care and nephrology researchers. Also, clinics from Johns Hopkins, University of Michigan, Cleveland Clinic, Montefiore Medical Group, and Medical University of South Carolina are already enrolled.

**If you are interested in joining a pediatric quality improvement collaborative study to improve pediatric hypertension diagnosis and management, we would first and foremost ask that you identify a primary care practitioner(s) and a pediatric nephrologist or cardiologist who will be your co-leads for this study.** As much of this project is centered around the care delivered in primary care, the primary care co-leader will be essential to its success. We also **suggest that each subspecialist identify at least 2 (or more) clinics** who they can work with, as we want to make sure the subspecialist has a large enough hypertensive patient volume referred from the primary care clinics to make it worthwhile for them to participate.

**Once you have your partner(s), please reach out to me ([[contact]](mailto:[contact])) or join one of our introductory webinars:**

- Thursday August 30th 2-3PM EST
- Wednesday September 5th, 3-4PM EST
- Login information same for both dates:

Join from PC, Mac, Linux, iOS or Android: <[name]>

US: [contact] or [contact]

Meeting ID: [name]

Thank you again for your interest and all the best,

--[name]

